#### Follow-up surveys

The 3- and 6-month surveys will employ the same measures as those assessed at baseline using a past 3-month timeframe.

### Use of interventions

A count of participant logins into the intervention, as well as the various web pages accessed within the G-only intervention (as well as use of the CYD), will be available. These data will be used to investigate whether participants’ degree of involvement with the intervention is associated with their success at recovering from gambling or reducing gambling severity. The degree of G-only intervention use by participants will be operationalized according to the previously recommended methods [38, 39]. The number of times a participant accesses the site, the number of tools the participant uses (as assessed by page views, form completions, etc.), and the length of involvement with the site (e.g., use of the site over time) will be recorded.

### Power analysis

Efforts will be made to recruit a total sample of 280 participants, and we anticipate that 224 participants will be successfully followed up at 6 months (i.e., estimated 20% attrition based on previous research of online interventions, albeit targeting hazardous alcohol use) [40]. This sample size will provide sufficient power to conduct the proposed statistical analyses necessary to test the aforementioned hypotheses. Based upon previous data collected by Hodgins et al. [4, 6] on gambling frequency and NODS scores, and assuming that a correlation of 0.5 exists between baseline and follow-up measures, then power = .0.80 and α = .05. This sample size is sufficient to detect a difference of at least two gambling days per month between both experimental conditions in both the 3- and 6-month follow-up periods. Smaller differences in gambling days per month may not be clinically meaningful. Similarly, the proposed sample size will also be sufficiently powered to detect a 1-point difference of NODS scores at the 6-month follow-up. Calculations are based upon a repeated measures ANOVA model (G.Power 3.1.9).

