### Major research questions

The proposed trial will compare the efficacy of two Internet interventions: an intervention that just targets gambling issues (G-only) versus one that contains an intervention for problem drinking in addition to an intervention for gamblers (G + A). Outcome variables for gambling will measure the reduction in gambling severity and frequency of gambling. The outcome for a reduction in alcohol use will be measured by the reduction in the frequency of drinking during the past week. The primary hypotheses are:**Hypothesis 1:** For problem gamblers with co-occurring problem drinking, it is predicted that participants provided access to the G + A website will display significantly reduced gambling outcomes at the 3- and 6-month follow-ups compared to those provided access to the G-only website. For problem gamblers without co-occurring problem drinking, there will be no significant difference between those provided access to the G-only and G + A websites at the 3- and 6-month follow-ups.**Hypothesis 2:** For problem drinkers, it is predicted that participants provided access to the G + A website will display significantly reduced drinking outcomes at the 3- and 6-month follow-ups compared to those provided access to the G-only website. For participants who are not problem drinkers, there will be no significant difference in drinking between those provided access to the G-only and G + A websites at the 3- and 6-month follow-ups.**Hypothesis 3:** Problem gamblers with co-occurring problem drinking who receive the G + A intervention and reduce the amount they drink between the baseline and 3-month follow-ups will display significantly improved gambling outcomes at the 6-month follow-up compared to problem drinkers who receive the G + A intervention but experience no decrease in their drinking.

Follow-ups at 3 and 6 months were chosen as it is unknown whether the intervention will have the predicted impact, and we wished to optimize the possibility of finding an effect by employing a short-term follow-up.

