## Methods/design

### Participants

Participants will be recruited using a comprehensive online and in-print advertisement strategy targeting Manitoba residents (e.g., local newspaper ads, social media ads on Facebook, and website ads on Yahoo and Google AdWords restricted to Manitoba residents). Advertisements will target gamblers who self-identify as being concerned about their gambling and are interested in participating in a study that aims to “find ways to help people who are worried about their gambling.” Prospective participants, 18 years or older who report gambling in the past 30 days, will be directed to complete a brief web-based screener that assesses problem gambling severity. The eligibility of individuals will be determined by their willingness to be followed up, and a current score of 3 or more on the Problem Gambling Severity Index (PGSI) [21]. Prior treatment access will be measured; however, it will not be used to determine eligibility as the intent of this trial is to evaluate the impact of the interventions within a real-world community setting. Similarly, co-occurring depression, anxiety, and illicit drug consumption will be measured but will not be used as exclusion criteria. Finally, while recruitment is not specifically targeted to attract problem drinking, it is anticipated that the trial will contain participants with and without co-occurring problem drinking. Based on the frequency of co-occurring problem drinking and gambling in the general population, it is estimated that approximately 50% of the sample will have co-occurring problem drinking [14, 22]. Participants in the first trial (examining the impact of combining an Internet intervention for gambling with one for mood and anxiety) will not be eligible to participate in the current trial.

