## Discussion

Many problem gamblers are also problem drinkers [13, 14, 17–20], with a lifetime prevalence as measured by nationally representative samples ranging from 45% to 73% [14, 22]. Heavy drinking often occurs while problem gamblers are engaging in gambling activities [42], resulting in increased risky gambling behavior [43–45]. Further, co-occurring problem drinking negatively impacts the treatment outcomes of problem gamblers (see the systematic review by Merkouris et al. [46]). Targeting problem drinking by problem gamblers may have the dual benefits of reducing both the problem drinking itself and of acting as a mediator for reductions in problem gambling behavior.

The proposed study seeks to determine whether providing simultaneous Internet interventions for gambling and drinking is of benefit for those with these co-occurring problems. More specifically, it will evaluate whether there is an incremental benefit to providing access to a problem drinking Internet intervention (G + A intervention) in addition to an Internet intervention for problem gambling (G-only intervention) for individuals with gambling problems who do or do not have co-occurring problem drinking. A limitation of the current trial is its short follow-up period (6-month follow-up). If the trial finds that the addition of a brief alcohol intervention to an online gambling intervention is beneficial at this time point, then future research examining any sustained impact of the intervention would be merited. The results of this study will enhance our understanding of Internet interventions for addictions in general, as well as inform how treatments can be developed and matched to the care of and needs for those with co-occurring problem gambling and drinking.

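### The stated 80% power is not shown to apply to problem drinkers, where H1 predicts its benefit; if it is a whole-sample figure, power in that half is about 51%

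*Protocol article*

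**What the plan says.** The Power analysis section gives the numbers, with the follow-up time in months: "Efforts will be made to recruit a total sample of 280 participants, and we anticipate that 224 participants will be successfully followed up at 6". The loss is an "estimated 20% attrition based on previous research of online interventions". The settings are given as "assuming that a correlation of 0.5 exists between baseline and follow-up measures, then power = .0.80 and α = .05", which I read as power 0.80. The targets are 2 gambling days per month and 1 NODS point: "This sample size is sufficient to detect a difference of at least two gambling days per month between both experimental conditions". The model is named only as a repeated measures ANOVA. The section then extends its conclusion to every hypothesis: "This sample size will provide sufficient power to conduct the proposed statistical analyses necessary to test the aforementioned hypotheses".

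Major research questions places the predicted gambling benefit in one stratum: "For problem gamblers with co-occurring problem drinking, it is predicted that participants provided access to the" combined (G + A) website will do better. For participants without problem drinking, the same hypothesis predicts no significant difference. Hypothesis 2 has the same two-part form for drinking outcomes. Hypothesis 3 is confined to problem drinkers who received G + A.

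On the size of that stratum, the Participants section says "it is estimated that approximately 50% of the sample will have co-occurring problem drinking". The Discussion describes the two sources cited for this as giving figures "with a lifetime prevalence as measured by nationally representative samples ranging from 45% to 73" per cent. The Baseline survey section defines problem drinking in the trial differently, as a score of 8 or more on a past-3-month AUDIT.

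**The concern.** The population in the power statement and the population in the lead hypothesis do not match. The Power analysis names one sample size and one contrast, between the two arms. It mentions no drinking subgroup, no subgroup size and no interaction. The benefit that H1 predicts exists only in about half of those participants, so the contrast that tests it has about half the information.

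The same section treats differences below 2 days per month as possibly not clinically meaningful, so 2 days is the plan's own threshold. If the subgroup has only about an even chance of showing a true 2-day difference, a non-significant result in problem drinkers would say little about whether G + A helps them. A reader relying on the 80% would think it said much more. The second half of H1 has a related weakness: with a similar number of non-problem drinkers, a true 2-day difference there would be non-significant about 49% of the time, so the predicted absence of a difference could appear by chance.

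**Working it through.** **Inputs.** From Power analysis: 280 recruited, 20% attrition, 224 followed up, power 0.80, α = 0.05, targets of 2 days per month and 1 NODS point. From Participants: problem-drinker share p of about 0.50. From the Discussion: lifetime range 45–73%. Assumptions, because the article does not state them: two-sided test, 1:1 allocation, the same share and attrition in each arm, and the same SD in problem drinkers as overall.

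**The plan's own figures.** 280 × 0.80 = 224, so the attrition step reproduces. The 80% cannot be reproduced, because no SD, number of groups, number of measurements or tested term is given. I therefore take 80% at 224 (112 per arm) as true and scale it.

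**Scaling.** The noncentrality for 80% power at two-sided 0.05 is 1.960 + 0.842 = 2.802. For a fixed difference and SD it is proportional to the square root of the number analysed, so in a subgroup of share p it is 2.802 × √p, and power ≈ Φ(2.802√p − 1.960). The unknown SD cancels. The detectable difference at 80% power is the stated target divided by √p.

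At p = 0.50, 224 × 0.50 = 112 followed up, 56 per arm. The noncentrality is 2.802 × 0.7071 = 1.981, and power is Φ(0.021) = 0.508.

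| Problem-drinker share | Noncentrality | Power | Detectable at 80%: days per month | NODS points |
|---|---|---|---|---|
| 45% | 1.880 | 0.47 | 2.98 | 1.49 |
| 50% | 1.981 | 0.51 | 2.83 | 1.41 |
| 60% | 2.170 | 0.58 | 2.58 | 1.29 |
| 73% | 2.394 | 0.67 | 2.34 | 1.17 |

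The 60% row is only an intermediate point. Below 45% the figure falls further; an assumed share of 40%, which has no source in the article, gives 2.802 × 0.6325 = 1.772 and power 0.43.

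**Checks at p = 0.50.**
- Noncentral F instead of the normal approximation: 0.505.
- Two-group repeated measures ANOVA formulas (between-group and group-by-time terms, 2 or 3 measurements, correlation 0.5): 0.485 to 0.505.
- Base of 280 instead of 224: again 0.51.
- One-sided α of 0.05: (1.645 + 0.842) × 0.7071 = 1.758, and Φ(1.758 − 1.645) = 0.55.

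**SDs implied by each reading.** If the 80% holds at 224, the standardized difference is 0.376, so the SD is 2/0.376 ≈ 5.3 days and 1/0.376 ≈ 2.7 NODS points when the correlation gives no gain. These rise to about 6.5 and 3.3 under the most favourable repeated-measures use of the 0.5 correlation. If the 80% was instead computed for 112 problem drinkers, the implied SDs are about 3.7–4.6 days and 1.9–2.3 points. The authors can see from their own SDs which reading applies.

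**Supplementary.** An arm-by-problem-drinking interaction of 2 days (2 days in drinkers, none in the rest) at p = 0.50 has noncentrality 2.802 × √(0.5 × 0.5) = 1.401 and power of about 0.29. H1 is not worded as an interaction test, so this is context and not a shortfall against a stated claim.

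**The case against.** The strongest reply is that the article never says the 80% is a whole-sample figure. It is a condensed article and gives neither the SD nor the ANOVA settings. A calculation made for 112 problem drinkers would leave the 80% intact, and one for a four-group model would give about 0.65 for the two-arm contrast in drinkers. This stands, and it makes the 51% conditional. It does not remove the point: only the total number and the two arms are named, and neither alternative is mentioned.

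A second reply is that the mixed models in Data analysis use all available data, not only the 224. The result is a ratio, so a base of 280 gives the same 51%.

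Third, the share could exceed 50%, since the article's own range reaches 73%. That is fair and is why the full range is shown; even at 73% power is about 0.67. The range is also a lifetime one, whereas the trial's definition is past 3 months. The article does not allow the size of any resulting shortfall to be judged.

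Stronger readings are tempting but not supported:
- A reader might infer that the 80% was miscalculated. Nothing shows that; the issue is which contrast it belongs to.
- A reader might say that H1 is tested only in problem drinkers. That is exact for its superiority part only, since H1 also makes a prediction for the others.
- A reader might attach a power figure to H3. The article gives neither the proportion expected to reduce drinking nor an effect size for that comparison, so any figure would rest on invented inputs.

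**Conclusion.** The point holds in conditional form. The article claims adequate power for all its hypotheses, but the only calculation it reports is, on its natural reading, for a contrast other than the one that tests H1's predicted benefit. On that reading, power in problem drinkers for 2 days per month or 1 NODS point is about 51% at the stated 50% share, and about 0.47 to 0.67 over 45–73%. It would be lower if fewer than 45% meet the trial's own AUDIT definition.

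This rests on the stated 80% being correct for 224 in a two-arm comparison, on a two-sided test and equal allocation, and on a common SD in drinkers and non-drinkers. It does not depend on the value of that SD. It is a scaling of the plan's figure, not an independent reproduction. For H2 (drinks per week) and H3 the finding is narrower: the article asserts sufficiency and gives no basis for it. That calculations may sit in a fuller document is no fault; the sentence claiming sufficiency is what needs correcting.

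**What to change.** In the Power analysis section:

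1. State the population, the SDs and the ANOVA term (groups, measurements, effect tested) behind the 80%.
2. Recompute with the authors' own SDs, and report power and the difference detectable at 80% power for G + A versus G-only within problem drinkers, for both NODS and gambling days. Do this over a range of problem-drinker shares that includes 50%, and note that the cited prevalence is lifetime while the trial's definition is past 3 months.
3. Remove the sentence claiming sufficiency for all hypotheses, or limit it to the contrasts for which a calculation is shown. If it is kept for H2 or H3, give the basis.

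The interaction power may be added as supplementary information. The 51% here shows the size of the problem; the published figure should come from the authors' own recalculation. The status of H1 need not change.

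The cost is a recalculation and a rewritten paragraph. No extra participants are needed. The stated power for the lead hypothesis will probably be less favourable, unless the 80% turns out to have been computed for the subgroup, in which case saying so settles the H1 part.

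### The 80% power is stated for all 224 followed-up participants, but Hypothesis 1 is tested in about 112 problem drinkers, where the same effect has about 51% power

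*Protocol article*

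**What the plan says.** All of this is in the protocol article.

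- **Power analysis, sample size.** The target is 280 recruited. After an expected 20% attrition, "we anticipate that 224 participants will be successfully followed up at 6 months".
- **Power analysis, error rates and correlation.** The calculation is made "assuming that a correlation of 0.5 exists between baseline and follow-up measures"; "then power = .0.80 and α = .05". The method is a repeated measures ANOVA in G*Power. No standard deviation is given for either outcome.
- **Power analysis, detectable differences.** For gambling days: "This sample size is sufficient to detect a difference of at least two gambling days per month between both experimental conditions", at both follow-ups. For NODS, the sample "will also be sufficiently powered to detect a 1-point difference of NODS scores at the 6-month follow-up". The section adds that smaller differences in gambling days might lack clinical meaning, and that the sample is enough to test the hypotheses set out earlier. It mentions neither a problem-drinking subgroup nor an interaction.
- **Major research questions, Hypothesis 1.** "For problem gamblers with co-occurring problem drinking, it is predicted that participants provided access to the G + A website" will have better gambling outcomes than those given G-only. In gamblers without problem drinking, no difference is predicted. The Abstract places the predicted benefit in the same subgroup.
- **Participants.** Recruitment does not target problem drinkers, and "it is estimated that approximately 50% of the sample will have co-occurring problem drinking".

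**The concern.** The power statement and the hypothesis it is meant to support refer to different numbers of people. The statement compares the two arms across everyone followed up. The superiority claim in Hypothesis 1 compares the arms only among problem drinkers, about half of them by the article's own estimate. An effect detectable with 80% power in a given sample is not detectable with 80% power in half of it.

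This matters most for reading a non-significant result. Readers told that the trial had 80% power would take it as evidence against adding the alcohol module. For gambling days, the article itself treats two days per month as roughly the smallest difference worth finding. If the real chance of detecting that difference in the relevant group is about one in two, a null finding says little.

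**Working it through.** **Inputs**

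- 280 recruited and 20% attrition: 280 × 0.80 = 224 followed up (Power analysis).
- Two arms (Study design and procedures). Equal allocation is assumed because the ratio is not stated: 112 per arm.
- α = .05, taken as two-sided (sidedness is not stated), and power 0.80 (Power analysis).
- Problem drinkers about 50% (Participants): 224 × 0.50 = 112, or 56 per arm.
- Differences: two days per month, one NODS point (Power analysis).

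**Step 1: the plan's own figure.** Without a standard deviation, the 80% cannot be derived forward. It can be taken as true for 112 per arm and solved for the standardized difference d that it implies:

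- Normal approximation: d = (1.960 + 0.842) × √(2/112) = 0.374.
- Noncentral t: d = 0.376.

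On an unadjusted two-group comparison this means an SD of 2/0.376 = 5.3 days, or 1/0.376 = 2.7 NODS points. Other model options imply different SDs (about 6.2 days and 3.1 points with baseline adjustment at correlation 0.5). The SD and the correlation are both absorbed into d, so the next step does not depend on them.

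**Step 2: the same effect in the Hypothesis 1 population, 56 per arm.**

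- Normal approximation: 0.374/√(2/56) − 1.960 = 0.021, so power = Φ(0.021) = 0.508.
- Noncentral t: 0.505.
- Repeated-measures F test of the group-by-time interaction (two measurements, correlation 0.5), set to 0.80 at N = 224: 0.505 at N = 112.

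**Step 3: what 56 per arm can detect with 80% power.** The noncentral t gives d = 0.534. The ratio 0.534/0.376 is 1.42 (√2 = 1.41 by the normal approximation). That is 2 × 1.42 = 2.8 days per month, or 1 × 1.42 = 1.4 NODS points.

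**Step 4: other ways to test Hypothesis 1.** Assume, as the hypothesis does, the full effect in drinkers and none in the others.

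- Whole-sample comparison: average effect 0.5 × 2 = 1 day, so d = 0.376/2 = 0.188 at 112 per arm; power 0.29.
- Arm-by-drinking interaction with 56 per cell: 0.374/√(4/56) − 1.960 = −0.559; power 0.29.

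**Step 5: sensitivity of the subgroup result (noncentral t).** The Discussion cites a lifetime prevalence of 45% to 73%.

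| Assumption | Power for two days or one NODS point |
|---|---|
| 45% problem drinkers | 0.46 |
| 50% | 0.50 to 0.51 |
| 60% | 0.58 |
| 73% | 0.67 |
| 50%, full information from all 140 randomized drinkers | 0.60 |
| 50%, baseline adjustment as a gain beyond the stated calculation (d/√0.75) | 0.62 |

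A one-sided test throughout gives 0.55 at 50% (normal approximation).

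**The case against.** The strongest objection is that the 51% is conditional. The article gives no SDs; they come from cited data that are not shown. The power section also says the sample is enough for the stated hypotheses, which literally include Hypothesis 1, so the calculation might have been run on 56 per arm. The implied unadjusted SDs would then be about 3.7 days and 1.9 NODS points, Hypothesis 1 would have 80% power, and whole-sample power would be about 98%. The documents do not strictly exclude this. But the section names only 280 and 224, refers to that sample size, and compares the two arms without mentioning a subgroup. If the subgroup had been used, the text would still have to say so.

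A second objection is that the mixed models use partly followed participants and the share of drinkers could be higher. Both raise power, but neither restores 0.80 (Step 5). Combining a 73% share with extra baseline adjustment reaches only 0.79, and that is generous, because the stated calculation already uses the 0.5 correlation.

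A third is that no arithmetic in the section is wrong, since 280 × 0.80 is 224. That is true: the fault is that the claim of sufficiency is attached to the wrong contrast. It is also fair that the remark on clinical meaning is hedged and concerns gambling days only; one NODS point is a detectable difference that the plan chose, not a stated clinical threshold.

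**Conclusion.** The concern holds. As written, the 80% power belongs to a whole-sample comparison, and the article wrongly extends it to Hypothesis 1. For the Hypothesis 1 contrast in problem drinkers, power for two gambling days per month or one NODS point is about 51%, and the differences detectable with 80% power are about 2.8 days or 1.4 NODS points. The whole-sample and interaction tests have about 29% power if the effect is confined to drinkers.

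These figures assume that the stated power is exactly 0.80 at 224, equal allocation, a two-sided test and 50% problem drinkers. They do not depend on the missing SDs. No share of drinkers in the 45% to 73% range that the article cites brings power back to 80%. Because this concerns a primary hypothesis, it should be corrected before the result is interpreted.

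**What to change.** Restate the power section for the contrast that Hypothesis 1 makes. Suggested wording:

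> Of 224 participants followed up, about 112 (56 per arm) are expected to be problem drinkers. For Hypothesis 1, power to detect two gambling days per month or one NODS point is about 51%; the difference detectable with 80% power is about 2.8 days or 1.4 NODS points. The 80% figure applies only to an effect that is uniform across the whole sample.

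The sponsor holds the planning SDs, so it should confirm these figures from them and state which population the 80% was computed for. The claim that the sample is sufficient for Hypothesis 1 at two days or one point should be dropped. The plan should also commit to reporting the Hypothesis 1 difference in problem drinkers with a 95% confidence interval read against two days and one NODS point, so that a non-significant result is not taken as no benefit.

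This costs wording and a less favourable stated power; it needs no new participants or data. For scale, keeping 80% power at two days or one point would take 224 followed-up problem drinkers: 224/0.50 = 448 followed up, and 448/0.80 = 560 randomized. The fix does not ask for that.
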